### Methods for additional analyses (e.g., subgroup analyses)

Subgroup analyses will not be conducted. However, we will apply sensitivity analysis of per-protocol analysis to assess potential biases.

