### Randomization

Patients will be randomly assigned to arm A (gasless TLRH) or arm B(TARH) in a 1:1 ratio by an internet-based distant third-party statistician blinded to the study and participant details. The doctor involved in recruitment will receive training and instructions on the recruitment procedure [18]. Only in case of a serious adverse event unblinding is permissible.

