### Sample size

The main purpose of this study is to determine whether gasless laparoscopic radical hysterectomy (gasless TLRH) or equivalent to total abdominal hysterectomy (TARH) is effective in terms of disease-free survival at 4.5 years. If the difference in disease-free survival rate does not exceed 7%, then these two surgeries are considered equivalent.

The estimated 4.5-year disease-free survival rate of patients receiving TARH is 90%. The sample size was based on an expected disease-free survival rate of 90% in the open-surgery group at 4.5 years and a noninferiority margin of 7.2 percentage points for minimally invasive surgery, which reflected an acceptable difference in the expected survival rate of at most 8 percentage points. In previous studies involving patients with other types of cancer, a noninferiority margin of 6 to 8 percentage points has been considered to be clinically acceptable.

Based on these data, a total of 740 patients (370 in each group) will be sufficient to declare equivalence in 4.5 years of accrual and 4.5 years of follow-up, with an equivalence margin of 6% or less at 4.5 years [8].

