### Statistical analysis

The main endpoint will be analyzed based on the intention-to-treat principle.

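### The equivalence claim rests on intention-to-treat alone, and the planned per-protocol analysis has no stated role in the decision

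*Protocol article*

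**What the plan says.** The Sample size section sets the aim as equivalence: "If the difference in disease-free survival rate does not exceed 7%, then these two surgeries are considered equivalent". The same section also gives "a noninferiority margin of 7.2 percentage points for minimally invasive surgery".

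The roles of the analysis sets are fixed in three places of the protocol article:

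- Statistical analysis: "The main endpoint will be analyzed based on the intention-to-treat principle".
- Phase II analysis: all efficacy comparisons are by ITT in everyone randomised, while toxicity is analysed by the treatment received.
- Methods for additional analyses: "we will apply sensitivity analysis of per-protocol analysis to assess potential biases". The Discussion repeats this as a means of limiting bias.

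The Phase 1 analysis reviews compliance with allocation after 100 patients, as one condition for going on. It gives no threshold. No section gives an expected rate of crossover or conversion, or says what follows if the ITT and per-protocol results disagree.

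**The concern.** Using ITT as the primary basis, with per-protocol as a sensitivity check, is the usual arrangement for a superiority trial. There, non-adherence shrinks the observed effect and works against the claim. Here the claim is that the arms do not differ by more than a margin, so the same shrinkage works for it. A patient allocated to arm A (gasless laparoscopy) who has the open operation contributes an open-surgery outcome to arm A and hides part of any true deficit.

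Departures from allocation are possible on the protocol's own terms. The trial is open-label. The Introduction reports a sixfold risk of death after minimally invasive surgery in an earlier randomised trial. The plan itself provides for a compliance review and for a toxicity analysis by treatment received.

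At stake is the chance of declaring equivalent an operation whose cancer control is worse by the full margin. As the rule is written, an ITT result inside the margin would support the claim even if the per-protocol result lay outside it.

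**Working it through.** **Inputs from the protocol article**

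- Open-surgery DFS at 4.5 years: "expected disease-free survival rate of 90% in the open-surgery group at 4.5 years".
- Margin M: 7.2 points for the main calculation. The Sample size section also mentions 6, 7 and 8 points, so 6 and 8 are used as a check.
- Size: "a total of 740 patients (370 in each group) will be sufficient to declare equivalence".
- Reporting: differences come with a 95% confidence interval (Phase II analysis).

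**Assumptions, not in the article**

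- One-sided alpha 0.025, matching the 95% interval, and 90% power.
- The claim is made when the upper 95% limit for the deficit is below M.
- The outcome follows the operation received, and a fraction c of arm A has the open operation (c = 0 to 20%).

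**Step 1: the plan's own figure.** With 90% DFS in both arms, n per arm = (0.9×0.1 + 0.9×0.1) × (1.960 + 1.282)² / 0.072² = 0.18 × 10.51 / 0.005184 ≈ 365. That is within 2% of the stated 370. Other combinations of margin, alpha and power also come close, so this shows only that 7.2 points with these error rates is a plausible reading. The 6-point margin does not reproduce 370 at one-sided 0.025: it needs 393 per arm at 80% power and 526 at 90%.

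**Step 2: dilution.** Let the true deficit equal M = 7.2 points.

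- ITT deficit: d = 7.2 × (1 − c).
- Arm A DFS under ITT: q = 0.90 − d.
- SE = √[(0.09 + q(1 − q)) / 370].
- False-claim rate = Φ[(0.072 − d)/SE − 1.96].

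| c | d (points) | q | SE | (0.072 − d)/SE | False-claim rate |
|---|---|---|---|---|---|
| 0 | 7.20 | 0.8280 | 0.0251 | 0 | 2.5% |
| 5% | 6.84 | 0.8316 | 0.0249 | 0.144 | 3.5% |
| 10% | 6.48 | 0.8352 | 0.0248 | 0.290 | 4.7% |
| 20% | 5.76 | 0.8424 | 0.0245 | 0.587 | 8.5% |

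**Step 3: sensitivity.** With 10% switching and the true deficit again placed at the margin, the rate is 4.3% for a 6-point margin and 5.0% for 8 points. The result therefore does not depend on which margin is adopted. Switching of 10% in both directions at 7.2 points gives a deficit of 5.76 points and a rate of 8.3%.

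**Step 4: power if per-protocol must also meet the margin.** With no true difference, power = Φ[0.072/√(0.18/n) − 1.96].

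- n = 370: Φ(3.264 − 1.96) = 90%.
- n = 352 (5% excluded): Φ(3.184 − 1.96) = 89%.
- n = 333 (10% excluded): Φ(3.097 − 1.96) = 87%.

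Power to pass both analyses cannot exceed the smaller of the two. Because the two sets share most of their patients, it should lie close to that figure.

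**The case against.** **A per-protocol analysis is planned.** A reader might infer that it has no bearing on the conclusion at all. The document does not support that: the analysis is planned expressly to look for bias, so it informs how robust the result is. What is absent is a role in the decision.

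**The analysis plan is not shown.** The definition of the per-protocol set and the handling of discordant results may be settled there, and their absence from an article is not a fault. It would also be wrong to criticise a set defined by the operation completed, because the article never proposes one. What stands is narrower: the article itself assigns the roles, with ITT as the basis and per-protocol as sensitivity.

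**Switching may be rare.** A reader might infer that arm A patients will ask for open surgery. Nothing documents this. The sixfold risk concerns conventional minimally invasive surgery, not the modified operation. Patients consent with time to reflect and can decline entry, one surgeon experienced in both approaches does every operation, and the review at 100 patients could expose heavy switching. These points make the 20% scenario less likely. They do not change the direction of the bias.

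**The calculation is unfavourable to the plan.** It puts the true deficit at the margin and gives every switcher 90% DFS. The first is the standard point at which to judge false-claim risk. The second may overstate dilution if switchers are difficult cases.

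**Per-protocol is not free of bias.** It excludes patients after randomisation. That is a reason to require agreement of both sets, not to replace ITT.

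**Conclusion.** The point holds in this limited form. The stated basis for the claim is ITT alone, ITT is not the conservative set for a no-worse claim when patients may receive the other arm's operation, and the per-protocol analysis has no stated part in the decision.

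The size rests on an assumed switching rate. It is minor at 5%. At 10% the false-claim rate nearly doubles, and at 20% it more than triples. These figures assume a true deficit at the margin, one-way switching and a decision by the 95% confidence interval.

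The documents do not show that switching will be common or that a false claim is likely. This is a worthwhile and cheap strengthening of the decision rule, not a defect that invalidates the design.

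**What to change.** In Statistical analysis and in Methods for additional analyses, state that equivalence or non-inferiority is claimed only if the confidence bound meets one chosen margin in both the ITT and the per-protocol analysis. The Sample size section must first settle on a single margin.

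Define the per-protocol set by the operation begun: eligible patients in whom the allocated operation was started. Patients converted during surgery, and those whose hysterectomy was abandoned for positive nodes as the protocol directs, stay in their randomised arm. Exclusions then do not depend on how the surgery went. Patients who changed approach before incision, or who never had surgery, are left out.

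This set does not remove dilution from conversions, so report, by arm, the number of conversions and of changes before incision. Table 1 already schedules the surgical treatment and operative details, so little new data collection should be needed.

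Cost: an amendment to the decision rule, best made before comparative results are known, and a small loss of power because two analyses must agree (Step 4 of the working). No change to the sample size is proposed.

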## Discussion

This trial is expected to provide high-level evidence that laparoscopic radical hysterectomy with a closed cervical cancer body, no lifting of the uterus, and no pneumoperitoneum may be a valid alternative to abdominal surgery with equal DFS and OS and superior short-term well-being for women diagnosed with early-stage cervical cancer.

It is reported that the continuously perfusing and flowing carbon dioxide in the abdominopelvic cavity could lead to the spread of the detached tumor cells [12, 13, 16]. Gasless laparoscopic surgery (GLS) is an effective operation in the treatment of gynecological diseases with few complications [20].

Investigated the usefulness of GLS using a subcutaneous abdominal wall lifting method for endometrial cancer.GLS for endometrial cancer results in less bleeding, shorter hospital stay, and fewer complications than open surgery. Recurrence and survival rates were not significantly different from those of open surgery [21]. Regardless of whether the CO_2_ pneumoperitoneum environment increased tumor cell growth or spread, our gasless laparoscopy was similar to laparotomy, which may be a protective measure. In the space formed by the suspension of the abdominal wall, the abdominal pressure is consistent with atmospheric pressure, which has little influence on the movement of the diaphragm, reduces the inflow of CO_2_ into the blood, and affects the blood gas. Eliminating the effects and risks related to CO_2_ has higher safety and is less likely to cause significant reactions to the respiratory and circulatory systems.

Andreas Kavallaris et al. retrospective 32 patients with stage FIGO (2009) IB cervical cancer underwent laparoscopic radical hysterectomy without the use of any uterine manipulator. This study showed a better tumor prognosis compared to studies using a minimally invasive approach with routine use of uterine manipulators and no vaginal closure of tumors [22]. In 2020, a large-scale cohort observation study SUCCOR showed that MIRH using different techniques (including avoiding uterine manipulators) yielded comparable results to existing techniques [23]. Therefore, compared to open surgery, cancer cell leakage may lead to poorer tumor prognosis.

All reported studies are retrospective designs, and most have not adjusted for confounding factors. In the future, high-quality prospective studies must be considered to validate the skills of surgeons. There are currently two ongoing clinical trials, including JGOG1087, a non-randomized controlled LRH trial in Japan aimed at preventing cancer cell overflow, and SOLUTION, a phase 2 non-inferiority trial evaluating the oncological outcomes of MIS using endoscopic sutures as a tool for preventing cancer cell overflow [24].

Retrospective case series on the laparoscopic treatment of early cervical cancer without pneumoperitoneum and uterine manipulator have been published. In addition, a number of prospective, randomized, and non-randomized clinical trials of the treatment of cervical cancer with different surgical pathways are ongoing. Trial NCT04999696 (ClinicalTrial.gov) is Minimally Invasive Therapy Versus Open Radical Hysterectomy for Management of Early Stage Cervical Cancer. This study aims to compare the differences in disease-free survival and overall survival between laparoscopic total hysterectomy and open total hysterectomy. Recurrence rates and characteristics, complications and incidence rate, impact on quality of life and cost-effectiveness will also be determined.820 people were included, covering the period from 2023 to 2033. Trial NCT03955185 is Clinical Trial of Minimally Invasive Surgery Versus Abdominal Surgery in Patients With Early Stage Cervical Cancer (RWS-01). They plan to recruit 2000 early cervical cancer patients from 20 to 30 selected surgical hospitals nationwide and have qualified and experienced doctors perform surgeries on the patients. They will provide detailed information on the patient's current research status and divide them into different observation groups based on their choice of surgical method. Close follow-up will be conducted on patients after surgery. They will compare the clinical outcomes of the two surgical methods and conduct subgroup and stratified analyses. We hope that this study can truly reflect the actual situation and clinical level of early cervical cancer treatment in China, and provide high-level clinical evidence for the treatment of cervical cancer in China.NCT04939831、NCT04929769、NCT04934982 through a multicenter stratified randomized controlled study, comparing different stages of cervical cancer, laparoscopic or abdominal radical hysterectomy for PFS and OS of patients with early cervical. Explore whether stricter surgical detail specifications (including tumor-free principles and standard surgical scope) can improve the PFS and OS of LRH, evaluate postoperative complications, and quality of life.

This proposed trial has strengths and weaknesses. A marked strength is that no high-quality studies are comparing the efficacy of gasless laparoscopic or abdominal surgery in the treatment of early cervical cancer. The current research experiments include ChiCTR2200064194, vaginal assisted single port laparoscopic radical surgery for cervical cancer using pneumoperitoneum and non-pneumoperitoneum: a prospective randomized controlled study. ChiCTR20000376, a randomized controlled study on the efficacy and safety of transumbilical single-hole laparoscopic surgery and traditional multi-hole laparoscopic surgery for cervical cancer. ChiCTR2100045060, a prospective randomized controlled study of robot and laparoscopic radical cervical cancer surgery. At present, there is no comparison of the clinical efficacy, safety, and clinical value between gasless laparoscopy and open surgery. If the outcome of gasless laparoscopy is the same as or better than open surgery, so this procedure had the advantages of all minimally invasive approaches, such as fast recovery and esthetic advantages. Strengths of our work also include its prospective design, standardized treatment protocol, and long duration of follow-up.

A limitation of this trial is that the design is not that of a confirmatory trial. Evaluation of the overall survival rate and recurrence rates, which are associated with the primary endpoint, will be performed by a clinical review board. The evaluation will be conducted under blind and independent conditions. And we will apply sensitivity analysis of per-protocol analysis to assess potential biases. Therefore, we believe that it will be possible to maintain objectivity and reduce potential bias. In addition, this is a single-center, randomized controlled trial design, although the operation is easy to operate and can be widely applied for gynecologists who have the foundation of traditional open cervical cancer surgery and laparoscopic surgery, in the future, we need multicenter, prospective studies to draw further strong conclusions.

We hope that the current study will increase the level of evidence on the comparison of tumor outcomes between gasless laparoscopy and open cervical surgery. We hope that “Laparoscopic radical hysterectomy with closed cervical cancer body and no lifting of uterus and no pneumoperitoneum,” that is, laparoscopy based on the open status has an encouraging survival outcome in the treatment of early cervical cancer, while improving the quality of life of patients. It is necessary to scientifically prove the efficacy of these surgical procedures in high-quality studies. We believe that the results of these studies will be important for the future direction of minimally invasive surgery.

### Trial status

This study protocol was approved on May 2023. The current protocol is version 1. The first patient is planned to be randomized on September 2023 and the expected end of recruitment is October 2028.

## Data Availability

Requests for data generated during this study will be considered by DMC. Data will typically be available within 6 months after the primary publication. Only scientifically sound proposals from appropriately qualified Research Groups will be considered for data sharing. The request will be reviewed by the Data Sharing Committee in discussion with the Chief Investigator and, where appropriate (or in the absence of the Chief Investigator) any of the following: the Trial Sponsor, the relevant Trial Management Group (TMG), and independent Trial Steering Committee (TSC). A formal Data Sharing Agreement (DSA) may be required between respective organizations once the release of the data is approved and before data can be released. Data will be fully deidentified (anonymized) unless the DSA covers the transfer of patient identifiable information. Any data transfer will use a secure and encrypted method. The authors promise to provide the original data supporting this study without reservation (provided by [name], email: [name][contact]).

## Abbreviations

DFS: Disease-free survival
OS: Overall survival
MIS: Minimally invasive surgery
LACC: Laparoscopic Approach to Cervical Cancer
SCD: Sequential compression device
LRH: Laparoscopic radical hysterectomy
SOP: Standard operating procedure
QOL: Quality of life instruments
DMC: Data monitoring committee
EDC: Electronic Data Capture System
TARH: Total abdominal hysterectomy
RWS: Real-world study
GLS: Gasless laparoscopic surgery
